### 2.3. Randomization

This is a single-center clinical trial with a sample size of 480. They were randomly divided into three groups equally. The randomization code will be developed by the statistics office of Dongzhimen Hospital. The trial cases were separated into three arms. The research pharmacy will randomize the participants based on the master randomization list. A third party will join to ensure the allocation concealment.

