### 2.10. Data Management and Statistical Analysis Plan

We use EDC system to collect the data. The system administrator establishes the eCRF and conducts logic verification and range checks for data values. Two investigators fulfill double-data entry.

The analysis will be performed in a modified intention-treat population, which included all randomized participants who received at least one dose of Xuesaitong or aspirin. Continuous variables are presented as the mean ± SD and categorical variables as number and percentage. Comparisons between treatment groups were assessed using Student's *t*-test or Wilcoxon rank-sum test for continuous variables. Comparisons were assessed using the Fisher exact test for categorical variables. Data for patients who were lost to follow-up were censored at the time of the last contact. A multivariable Cox proportional-hazards regression analysis that included center and treatment as independent variables was conducted, and the results are expressed as hazard ratio (HR) with 95% confidence interval (CI). The incidence of adverse events was compared using the chi-squared test. *P* < 0.05 (two-sided) was considered to be statistically significant. All analyses were conducted using SPSS software 26.0.

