(1) Serious adverse events occur or having obvious abnormal value of the laboratory tests
(2) The investigators believe someone's trial needs to be terminated because of medical, safety, or GCP considerations
Trial termination
(1) Half of the participants have mild adverse events other than gastrointestinal reactions
(2) The investigators believe it is necessary to abort the trial for medical or safety purposes

**Table 3 tab3:** Dose and duration of medication.

Group	Medication	Dose and method	Duration
Aspirin group	Enteric-coated aspirin	100 mg, q.d., oral	30 days
Xuesaitong group	Xuesaitong soft capsule	200 mg, t.i.d., oral	30 days
Drug combination group	Xuesaitong soft capsule + enteric-coated aspirin	100 mg q.d. oral aspirin and 200 mg t.i.d. oral Xuesaitong soft capsule	30 days

**Table 4 tab4:** Clinical outcomes of the trial.

Items
*Primary outcomes*
Primary outcomes of improving efficacy
Platelet aggregation rate (platelet aggregation analyzer)
Primary outcomes of reducing gastrointestinal side effects
Change in calprotectin activity (ELISA) [17]

*Secondary outcomes*
Secondary outcomes of improving efficacy
(1) Change in PAC-1 activity (flow cytometry)
(2) Change in P-selectin activity (flow cytometry)
(3) Change in P2Y12 acceptor activity (flow cytometry)
Secondary outcomes of reducing gastrointestinal side effects
(1) Change in I-FABP activity (ELISA) [18]
(2) Change in fecal occult blood

*Safety outcomes*
(1) Serum biochemistry
(2) Blood routine
(3) Urine routine
(4) Stool routine
(5) ECG

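### The only regression planned is a Cox model with centre as a covariate and censoring at last contact, but the trial has one centre and no listed outcome is a time to event

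*Protocol article*

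**What the plan says.** Section 2.10 gives these analysis methods:

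- Continuous variables: "Comparisons between treatment groups were assessed using Student's *t*-test or Wilcoxon rank-sum test for continuous variables".
- Categorical variables: "Comparisons were assessed using the Fisher exact test for categorical variables".
- Loss to follow-up: "Data for patients who were lost to follow-up were censored at the time of the last contact".
- Regression: "A multivariable Cox proportional-hazards regression analysis that included center and treatment as independent variables was conducted".
- Effect measure reported from that regression: "the results are expressed as hazard ratio (HR) with 95% confidence interval (CI").
- Adverse events: "The incidence of adverse events was compared using the chi-squared test".

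On the number of centres, Section 2.3 says: "This is a single-center clinical trial with a sample size of 480". The Abstract and Section 2.1 agree.

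Table 4 lists the outcomes. The first primary outcome is "Platelet aggregation rate (platelet aggregation analyzer"), and the second is the change in calprotectin. Section 2.1 and Table 1 place the blood and stool biomarkers on day 1 and day 30 only.

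**The concern.** A Cox model needs an event, a time origin and follow-up during which the event may or may not occur. Section 2.10 supplies none of these and names no outcome for the model. It also adjusts for a factor that does not vary in this trial.

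What is at stake is mainly estimation. The article's title, Introduction and Discussion call this a noninferiority trial, and noninferiority is normally judged from a confidence interval for the difference between arms. The hazard ratio is the only quantity for which Section 2.10 promises an interval. The other methods are stated as tests, with a two-sided 0.05 threshold for P. If the hazard ratio cannot be computed, the article names no usable effect estimate with an interval for either primary outcome.

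**Working it through.** No figure in the plan has to be reproduced here. The check sets the stated model against the stated design.

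**1. Is any outcome a time to event?** Count from Table 4:

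| Class | Number | Content | Time to event |
|---|---|---|---|
| Primary | 2 | platelet aggregation, calprotectin | 0 |
| Secondary | 5 | PAC-1, P-selectin, P2Y12, I-FABP, fecal occult blood | 0 |
| Safety | 5 | serum biochemistry, blood, urine and stool routine, ECG | 0 |
| Total | 2 + 5 + 5 = 12 | | 0 |

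The secondary outcomes are all listed as changes, including fecal occult blood. The article gives no event definition, time origin, hazard ratio or number of events. The sample size in Section 2.4 rests on platelet aggregation rates (38.72% and 37.79%).

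**2. Can centre be estimated?** The stated model is

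h(t) = h0(t) · exp(β · treatment + γ · centre).

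With one centre, centre = c for everyone. Each term of the partial likelihood is then

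exp(β·x_i + γ·c) / Σ_j exp(β·x_j + γ·c) = exp(β·x_i) / Σ_j exp(β·x_j).

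The factor exp(γ·c) cancels, so γ cannot be identified and the adjustment does nothing. Even if an event were defined, only treatment would remain in the model.

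**3. Does censoring apply to the biomarkers?** Censoring records that an event had not occurred by a known time. A laboratory value scheduled for day 30 has no such partial information. Table 1 has no visit between D1 and D30, and the only earlier biomarker reading is the baseline one. A participant who leaves before day 30 therefore has a missing day-30 value, not a censored one.

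**4. What is left?** The t-test or Wilcoxon test applies to the continuous outcomes, including both primary ones. Fisher's test covers categorical outcomes and the chi-squared test covers adverse-event incidence. All can be run. None is stated with an effect estimate and interval.

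**The case against.** The strongest defence is that the Cox model was meant for adverse events, which Section 2.9 says are monitored throughout. The text does not bear this out. Section 2.10 gives adverse events to a chi-squared test of incidence and names no event for the Cox model. The bleeding events in inclusion criterion 6 belong to the eligibility criterion on earlier aspirin use and are not a listed outcome.

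A second defence is that a separate analysis plan may supply the right models. It may add methods, but it cannot make the stated model fit a single-centre trial without event times. The point concerns text that is wrong as written, not detail left out.

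A third defence does stand. Section 2.10 never assigns the Cox model to the primary outcomes, and those have a workable test of their own. Removing the Cox sentence changes no primary comparison.

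Three stronger readings are tempting but not supported:

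- A reader might infer that the primary analysis cannot be carried out. It can, by t-test or Wilcoxon test.
- A reader might infer that the plan offers censoring as its answer to dropout, so that 20% of 480 = 96 day-30 values fall under an unworkable rule. The censoring sentence comes directly before the Cox sentence and reads as part of that model. The article does not say that it governs missing values in the t-test. The 20% is also a planning allowance, not an observed loss.
- A reader might infer bias from dropout that differs by arm, since the trial is open-label and one arm receives no aspirin after at least a year of regular use. This is plausible, but the article gives no dropout by arm, so neither size nor direction can be derived.

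**Conclusion.** The point holds in a limited form. The Cox model, hazard ratio, centre term and censoring rule are inconsistent with the article's own design: 0 of 12 listed outcomes is a time to event, and 1 centre leaves nothing to adjust for. The consequence is an unassigned regression that cannot be used, together with the loss of the only effect estimate for which an interval is named. It is not a failed primary analysis, and no bias in the primary outcomes has been shown.

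The conclusion rests on Table 4 being the full outcome list and on the trial staying at a single centre, as the article says it is.

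**What to change.** Delete the Cox model, the hazard ratio, the centre term and the censoring sentence from Section 2.10. In their place, for each continuous primary and secondary outcome, state a linear model of the day-30 value on treatment arm and the baseline value already collected, with calprotectin on the log scale if it is skewed. Report adjusted between-arm differences with 95% confidence intervals. With baseline in the model, the treatment effect is the same whether the response is the day-30 value or the change. Baseline adjustment also improves precision, by an amount that depends on the correlation between the two readings, which the article does not give. Fecal occult blood, if recorded as a category, can stay with its categorical test.

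State that participants without a day-30 value have missing data and are not censored. The modified intention-to-treat population can stay as defined, since this point shows no error in it. A likelihood-based or multiple-imputation analysis is an optional addition. If a sensitivity analysis shifts imputed values, the shift should be applied to each arm in turn, including the Xuesaitong-only arm.

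The cost is wording and a little analysis work. No new data, visits or participants are needed.

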Xuesaitong capsule is a marketed Chinese medicine with components of Panax notoginseng saponins (PNS), which is a mixture of ginsenosides Rb1, Rg1, Rd, Re, and notoginsenoside R1. It has been used in combination with aspirin in preventing cardiovascular disease for several years with a good clinical effect [7, 8]. Our previous study has indicated that the combination could inhibit platelet activation caused by blood hypercoagulability and reduce platelet aggregation to prevent thrombosis [9, 10]. These effects may rely on another finding from our team, which shows that aspirin and Xuesaitong could increase the area under the curve (AUC) and promote the absorption of each other [11, 12]. More interestingly, our research also found Xuesaitong attenuates expression of aspirin-induced tight junction protein and apoptosis of crypt epithelial cells in small intestine [13]. It means Xuesaitong may serve as a pharmacological treatment for aspirin-induced gastrointestinal injury. Since the dual-directional regulation of Xuesaitong, it became the potential combination therapy to solve the clinical dilemma. All the preclinical evidences have elucidated the combination could enhance aspirin's efficacy and decrease aspirin-induced gastrointestinal injury. However, it still lacks high-level clinical evidence.

In this study, we conducted a randomized controlled noninferiority trial to explore whether the efficacy and safety of combination for CHD patients are superior to the single use.

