## 2. Methods

### 2.1. Study Design and Setting

This is a prospectively planned, open-labeled, parallel-grouped, single-centered clinical trial. The trial will be conducted at the outpatient care of the Cardiology Department at the Dongzhimen Hospital, Beijing University of Chinese Medicine in China. The staff of the department will be informed of the trial and they will help researchers to recruit participants. The trial is conducted by the ethical principles laid down in the Declaration of Helsinki, the Guideline for Good Clinical Practice, and local laws. The informed consent form will be obtained from all participants before any trial-related procedures were conducted, enrolled after a complete and extensive description of the study. The trial was approved by the Ethics Committee of Dongzhimen Hospital, Beijing University of Chinese Medicine (Supplementary File 1). We present the protocol in accordance with the SPIRIT reporting checklist (Standard Protocol Items Recommendations for Interventional Trials) (Supplementary File 2).

In terms of research methods, we refer to and improve one of our previous experimental designs [14]. 480 participants will be randomly assigned to either an aspirin group, a Xuesaitong group, or drug combination group at a ratio of 1: 1: 1. Participants in the aspirin group will be administered aspirin (100 mg, qd) orally 30 min after breakfast, participants in the Xuesaitong group will be administered Xuesaitong soft capsule (contains PNS and excipients; 200 mg, tid) orally 30 min after breakfast, and participants in the drug combination group will be administered both drugs above. The two drugs should be taken half an hour apart, and aspirin should be taken first. All treatment courses will last for 30 days. Blood samples will be acquired 30 min before administration on day 1 and 30 min after administration on day 30. The volume of each blood sample is 4 mL. And fecal samples will be collected on days 1 and 30. Details of patient follow-up are summarized in Table 1 and Figure 1.

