### 2.4. Sample Size

The sample size was calculated based on the primary outcome (platelet aggregation rate). For power analysis, the primary outcome was assumed to be 38.72% in the aspirin group [15], and 37.79% in the Xuesaitong group [16]. Given a type I error at 0.05 and type II error at 0.2, the required sample size was 131 per arm. Expecting 20% dropout rate, we planned to enroll 160 subjects.

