Xuesaitong, a marketed Chinese medicine with the main active component of PNS, has been widely and long-term used to prevent and treat hematological diseases and cardiovascular diseases [23]. Several clinic trials indicated that Xuesaitong could inhibit platelet activation in patients with blood hyperviscosity syndrome [24]. Interestingly, as for the widespread clinical application together with aspirin, many clinicians found its ability to protect against gastrointestinal injury. In view of this protective efficacy, some researches have shown that Xuesaitong could enhance the proliferative ability of human endothelial cells to heal the wound and stop bleeding [25]. Our previous studies demonstrated Xuesaitong can alleviate gastrointestinal injury caused by aspirin in rats [13]. Combined with HE staining results, our results indicate that the protective mechanism of Xuesaitong on aspirin-induced gastrointestinal injury may act through increasing VEGFA and protecting gastrointestinal mucosa. As for Xuesaitong's ability that both effectively guarantee the clinical efficacy of aspirin and prevent gastrointestinal injury, it is worthwhile to further study the mechanism of the combination of these two drugs and supply a rational combination. Since we have proved that aspirin and Xuesaitong could increase the AUC of each other [11, 12], this means the content of effective drugs in the blood increased. In order to achieve the same blood concentration, the intake of aspirin might be reduced, the adverse reaction might also reduce accordingly. To explore the possibility of reducing the dose of aspirin, it is worth making clear the efficacy and safety of the combination of aspirin and Xuesaitong. By using this randomized controlled noninferiority trial, determining the clinical efficacy indexes like aggregation rate, platelet membrane glycoprotein indexes, and gastrointestinal injury indexes like calcitonin activity and I-FABP allows us to find out whether the platelet aggregation in patients was excessively inhibited and whether the digestive tract injury caused by aspirin is alleviated under drug combination.

In conclusion, the results of this study are expected to provide evidence of high methodological quality on the synergy effect of combination of Xuesaitong and aspirin for CHD synergy effect of combination of Xuesaitong and aspirin.

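### Adverse events are to be compared only by a chi-squared P value, with no between-arm difference or interval; for less common events a null result would not exclude a doubling

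*Protocol article*

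**What the plan says.** The Introduction states that the trial is to "explore whether the efficacy and safety of combination for CHD patients are superior to the single use". The Discussion returns to this: "it is worth making clear the efficacy and safety of the combination of aspirin and Xuesaitong".

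Section 2.4 fixes the size: "The sample size was calculated based on the primary outcome (platelet aggregation rate"). It arrives at 131 per arm with a type II error of 0.2, raised to 160 for 20% dropout. It gives no adverse-event rate and no power for adverse events.

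Section 2.10 fixes the comparison: "The incidence of adverse events was compared using the chi-squared test". The general threshold there is two-sided P < 0.05. The analysis set is "all randomized participants who received at least one dose of Xuesaitong or aspirin". Categorical variables are to be presented as counts and percentages, and the same section also says "Comparisons were assessed using the Fisher exact test for categorical variables". The only confidence interval named belongs to a Cox hazard ratio whose endpoint is not given.

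Table 4 lists calprotectin as a primary outcome and I-FABP and fecal occult blood as secondary outcomes, all under reduction of gastrointestinal side effects. The listed safety outcomes are laboratory tests and ECG.

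**The concern.** A significance test says whether a difference was detected. It does not say how large an excess of harm remains compatible with the data, and that is what a safety conclusion about adding one platelet-inhibiting drug to another needs. Sizing a trial on its primary outcome is normal practice, but it means that nothing here makes the adverse-event test sensitive to a relevant excess.

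The comparison matters most for clinical events that no listed outcome captures, such as bleeding outside the gut. For these the adverse-event test is the only between-arm comparison stated. The article itself gives reason to look closely: it reports that the two drugs raise each other's AUC, and it asks whether platelet aggregation might be inhibited too far. It also wants the efficacy and safety results to inform whether the aspirin dose could be reduced, so a null result that looked reassuring could be carried forward.

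**Working it through.** **No figure to reproduce.** The article states no power or sample size for adverse events, so the check starts from its stated sample sizes and significance level.

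**Inputs from the article**
- 480 randomised 1:1:1, so 480/3 = 160 per arm (section 2.1). The analysis set in section 2.10 keeps everyone dosed, so 160 is close to the planned denominator.
- 131 per arm required (section 2.4). Also 160 × 0.8 = 128 per arm, if the 20% who drop out contribute nothing.
- Two-sided α = 0.05 (section 2.10).

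**Assumption.** The 30-day adverse-event rate is not stated. I take a range of single-drug rates p₁ and a doubled combination rate p₂ = 2p₁. The long-term peptic ulcer figure in the Introduction is not a 30-day adverse-event rate and is not used.

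**Formula.** For the pairwise uncorrected chi-squared test, with p̄ = (p₁ + p₂)/2:

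power ≈ Φ{ [p₂ − p₁ − 1.96·√(2p̄(1−p̄)/n)] / √([p₁(1−p₁) + p₂(1−p₂)]/n) }

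- 5% vs 10%, n = 160: (0.05 − 1.96 × 0.02945)/0.02932 = −0.263; power 0.396.
- 5% vs 10%, n = 131: (0.05 − 1.96 × 0.03254)/0.03240 = −0.426; power 0.335.
- 10% vs 20%, n = 160: (0.10 − 1.96 × 0.03992)/0.03953 = 0.550; power 0.709.

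Exact binomial enumeration of the same test agrees closely (0.394, 0.335 and 0.714). Chance of missing the doubling, from the enumeration:

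| Single drug vs combination | n = 160 | n = 131 | n = 128 |
|---|---|---|---|
| 2% vs 4% | 83% | 86% | 86% |
| 3% vs 6% | 75% | 80% | 80% |
| 5% vs 10% | 61% | 66% | 67% |
| 10% vs 20% | 29% | 37% | 39% |
| 15% vs 30% | 10% | 16% | 17% |

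**Where the balance tips.** Solving the formula for power 0.5 gives p₁ = 6.5% (n = 160), 7.8% (n = 131) and 7.9% (n = 128). Power reaches 0.8 at about 12% (n = 160) and 14% (n = 131). For 80% power, 5% vs 10% would need 435 per arm and 10% vs 20% would need 199.

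**Other versions of the test**
- Fisher exact: power at 5% vs 10% is 0.32 (n = 160) and 0.25 (n = 131); at 10% vs 20% it is 0.66 and 0.56.
- Three-arm chi-squared test on 2 degrees of freedom with only the combination raised: 0.44 and 0.37 at 5% vs 10%; 0.78 and 0.69 at 10% vs 20%.

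The tipping point moves by a percentage point or so; the pattern does not change.

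**What an interval adds**
- Observed 16/160 vs 8/160: χ² = 320 × (16 × 152 − 8 × 144)² / (160 × 160 × 24 × 296) = 2.88, P = 0.09. The difference is 5.0 percentage points, with a Newcombe 95% CI of −0.9 to +11.1. The test reports no significant difference; the interval shows that an excess of 11 points is still compatible with the data.
- Identical counts of 8/160: upper 95% limit of the risk ratio = exp{1.96 × √(2/8 − 2/160)} = 2.6, so a doubling is not excluded even with no observed difference.
- Identical counts of 16/160: exp{1.96 × √(2/16 − 2/160)} = 1.9, so a doubling is just excluded.

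**The case against.** **The test works at higher rates.** A reader might infer that it misses a doubling at any common rate. The figures do not support that. At 10% vs 20% the doubling is found more often than missed under every version tried, and at 15% vs 30% it is missed only 10 to 17% of the time. Since the article gives no rate, nobody can say from it on which side of the 6.5% to 8% line the overall incidence will fall. This stands, and it limits the point to less common events. A low rate for separate categories is plausible over 30 days in people who have already taken aspirin for at least a year, but that is inference.

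**No misreading is planned.** A reader might also infer that the authors intend to treat P > 0.05 as evidence of safety. The article nowhere says so. Its stated aim is superiority, under which a null result would be a failure to show benefit. This stands too. But the trial is also labelled noninferiority, without tying that label to adverse events, so the reading of a null result is left open.

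**Safety does not rest on this test alone.** Calprotectin, I-FABP and fecal occult blood address gut injury; a DSMB, causality review and termination criteria address monitoring. It would be wrong to say that the chi-squared test carries the whole safety half of the aim. What remains is the final between-arm comparison of clinical events outside those measures.

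**The data for an interval will be there, and such detail can sit in an SAP.** Counts and percentages by arm will be reported, so any reader could compute a difference. Adverse-event categories and the interval method may fairly be left to a document not shown. However, the article does state its adverse-event rule, and a significance test alone is a weaker basis than an estimate with an interval.

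**Conclusion.** The point holds as a low-cost improvement to how clinical adverse events are compared. It is not an error in the sample size, nor evidence of a planned false safety claim. The stated rule yields a P value without a between-arm estimate or interval. If the single-drug rate is below about 6.5% (160 per arm) to 8% (about 130 per arm), a doubling is missed more often than found; at 10% the miss rate is 29 to 39%, which still exceeds the 20% type II error the trial accepts for its primary outcome. At 15% and above the test detects a doubling reliably.

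These figures rest on assumed event rates, on a doubling as the harm of interest, and on a pairwise comparison of the combination with one single-drug arm. The 160-per-arm figures fit the stated analysis set better; those for 131 and 128 show the effect of losses.

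**What to change.** In section 2.10:

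- Report the risk difference in adverse events, with a two-sided 95% confidence interval (for example Newcombe), for combination minus aspirin and for combination minus Xuesaitong.
- Base the safety conclusion on that interval, with better safety claimed only if the whole interval lies below zero.
- State that P > 0.05 will not be taken as evidence of equal or better safety.
- Keep the chi-squared P value as descriptive.

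This takes a few sentences and a few extra table columns, with no extra participants or data. The downside is a more cautious safety conclusion, because at these sizes the upper limits will often leave room for a sizeable excess.
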